### Recruitments

#### Sampling Methods

The method employed to sample radiographers is stratification followed by simple random sampling. The list of radiographers will be obtained from the radiographer in charge. After that, the inclusion and exclusion criteria will be applied to radiographers derived from the list. Then, radiographers will be stratified by gender, with male respondents representing 70% of the sample and female respondents forming 30%. After that, a software number generator will be used to select the targeted sample.

#### Matching

Matching has been used in research since the beginning of the 19th century [28]. Exact matching is the method that will be employed in this study. Stuart and Rubin [29] recommended the selection of the most common covariate that has an effect on the outcome in order to make matching possible. According to Loman [30], exact matching can be employed for up to 5 variables. Based on these principles, variables that underwent matching include gender, experience, education level, training, and the type of university from which a radiographer graduated.

Respondent characteristics will be obtained from the radiographers in charge in the control group. First, a sample from the intervention group will be randomly selected using a software number generator. Since the list of radiographers in the control group and the characteristics have already been obtained, exact matching can be performed. This method will help in making the groups comparable and similar in terms of confounder distribution.

### Sample Size

We will use the formula by Lemeshow et al [31] to estimate the minimum sample size required in intervention studies and to test a hypothesis of proportion of 2 population problems in terms of the radiographers sample size (see Figure 2), where *p* 1 and *p* 2 were obtained from a study by Moreira [32] to estimate the sample size of radiographers in each group and Z1–α=1.96, Z1–β=0.842, *p* 1 is 0.63, *p* 2 is 0.88, and *p*^–^=0.755. Figure 3 displays the sample size estimation of the secondary outcome variables.

According to Sullivan [33], the attrition rate (dropout) can be calculated by the formula (desired sample size)/(percent retained). Hence, for this study, a sample size of 56 for each group was targeted.

In terms of the repetition rate of routine digital chest radiographs sample size, the same formula was used, where *p* 1 and *p* 1 were obtained from the study of Zhang and Chu [34] to estimate the sample size of routine digital chest radiography in each group and Z1–α=1.96, Z1–β=0.842, *p* 1 is 0.0584, *p* 2 is 0.087, and *p*^–^=0.0728. Figure 4 displays the sample size estimation of the primary outcome variable.

According to Sullivan [33], the attrition rate that may occur due to any loss of chest images can be calculated by the formula (desired sample size)/(percent retained). The sample size of routine digital chest radiographs is 1618 for each group, and this number is expected to be reached within 2 weeks. Two weeks’ time is similar to that used in the study conducted by Ahmed and Suliman [35].

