## Introduction

Good quality images in routine radiography should provide an adequate picture of the body’s anatomy. Failure to obtain a good quality image requires the radiograph to be repeated. According to Foos et al [1], the term “repetition” refers to redoing a radiograph of a patient that was deemed clinically unacceptable. Repetition of an image is a critical event in radiology. It is recommended that the repetition rate should not exceed 5% [2-7]. The Diagnostic Imaging Quality Assurance Committee recommends that the repetition of radiographs should not exceed 5% to 7% [8]. The American Association of Physicists in Medicine recommends keeping the repetition rate below 6%, and when it increases to 10%, corrective action should be conducted [9]. The Australian College of Radiologists recommends an acceptable repetition rate of 2% and not more than 5% [10].

A study by Khafaji and Hagi [11] reported high repetition rates of radiography in Saudi hospitals, averaging 14.9%, which is higher than the international standard. Another study reported the repetition rate in 3 Ministry of Health hospitals ranged from 7.4% to 9.7%. The same study revealed that chest radiographs have higher repetition rates compared to other radiological procedures [12]. Related to that, it was revealed that radiographer error is one of the factors that strongly contribute to the issue of the repetition [13,14].

The production of high-quality images is based on radiographer practices. According to the World Health Organization, practice is influenced by the level of knowledge, motivation, and skills [15]. A study conducted in Saudi Arabia by Alsharif et al [16] showed that there is poor knowledge among radiographers in identifying image error. Another study conducted in Saudi Arabia by Ahmed et al [17] revealed that there is variation in radiographer knowledge of radiation protection, with 58% of radiographers indicating poor knowledge. Additionally, it was revealed that the motivation level of radiographers is low and this affects production of high-quality images [18]. Lack of knowledge and motivation dramatically influence skill level. It has been exhibited that the increase in repetition rate is due to deficiencies in radiographer skills [19]. Radiographers with high skills tend to avoid errors in the imaging process. Skills include the ability to communicate properly with the patient and handling the equipment accurately.

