## Methods

### Study Design

The design of this study is basically a quasi-experimental time series with a control group. This design was chosen because the intervention was recommended by other researchers [22,23]. A quasi-experimental study is the only design that could be applied in this study. The difficulty of randomizing by location and subject and the small number of the population make the quasi-experimental design suitable in this study [24]. In addition, there is difficulty in randomizing by subject to avoid potential contamination. Location is also a factor, since no 2 hospitals are similar.

The Makkah Region of Saudi Arabia was selected for the study because the problem has been ignored in the area and the repetition rate has not been periodically measured there [25,26]. Out of 5 hospitals, 4 will be selected to be in the study since randomization is not required in this type of study [27]. The hospitals involved are under the direction of Makkah Region health affairs. Two will be chosen as an intervention group and 2 as a control group. Preintervention assessment will be conducted in both groups at the same time during the second quarter of 2017. The intervention will be distributed to radiographers in the intervention group, and after 1 month, an assessment will be conducted. Six months after the implementation of intervention, a second postintervention assessment will be conducted. Figure 1 demonstrates the study flow.

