### Statistical Analysis

Data analysis in this study is divided into 2 parts: descriptive and inferential. Descriptive data will be calculated in order to compute the central tendency and dispersion to add valuable statistical information to the study. Inferential data analysis will be used to meet a specific objective. Chi-square, 1-way multivariate analysis of variance, 2-way repeated measure multivariate analysis of variance, and multivariate analysis of covariance are the statistical methods that will be used to test the hypothesis. *Cochran Q test* will be also employed to assess the difference in proportion. The level of significance will be set at α=0.05, and all testing of hypotheses will be conducted using 2-sided tailed hypotheses. The statistical program used is SPSS version 22 (IBM Corp).

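### The 1618 radiographs per group make no allowance for clustering within radiographers and hospitals, so the implied 80% power for the primary outcome holds only if radiographs are independent

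*Protocol article*

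**What the plan says.** All references are to the protocol article.

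- **Sample Size, method.** The radiographers are sized first with a formula for two proportions. For the primary outcome, "In terms of the repetition rate of routine digital chest radiographs sample size, the same formula was used", with "Z1–α=1.96, Z1–β=0.842" and repetition rates of 0.0584 and 0.087 (mean 0.0728).
- **Sample Size, loss and result.** An allowance for lost images follows, by the rule of desired size over percent retained; the text gives no percentage. Then: "The sample size of routine digital chest radiographs is 1618 for each group". The target for radiographers is 56 per group.
- **Study Design.** Four hospitals take part: "Two will be chosen as an intervention group and 2 as a control group". The section adds that hospitals differ from one another.
- **Abstract, Methods.** The images analysed are those taken by the sampled radiographers over 2 weeks before and after the intervention.
- **Introduction.** Radiographer error is named as one strong contributor to repetition. On differences between hospitals: "Another study reported the repetition rate in 3 Ministry of Health hospitals ranged from 7.4% to 9.7" percent.
- **Statistical Analysis.** "The level of significance will be set at α=0.05, and all testing of hypotheses will be conducted using 2-sided tailed hypotheses".

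**The concern.** The two-proportion formula counts every radiograph as a separate, independent observation. Here each group's images are nested twice: about 1618/56 = 28.9 per radiographer and 1618/2 = 809 per hospital. The module goes to radiographers in whole hospitals, so the comparison between groups is also a comparison between clusters. Repeats by one radiographer, or on one department's equipment, can be expected to resemble each other, and the article's own remarks on radiographer error and on differences between hospitals point that way.

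If such correlation exists, the effective number of observations is smaller than 1618 and the power is lower than the formula suggests. A non-significant primary result could then be read as evidence that the module does not work, when the study may have had little chance of showing that it does.

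**Working it through.** **1. Reproducing 1618.** Inputs from Sample Size: z-values 1.96 and 0.842, p1 = 0.0584, p2 = 0.087, mean p = 0.0728, difference d = 0.0286.

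n = [1.96·√(2·p·(1−p)) + 0.842·√(p1(1−p1) + p2(1−p2))]² / d²

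- First term: 1.96 × √(2 × 0.0728 × 0.9272) = 0.7202
- Second term: 0.842 × √(0.0550 + 0.0794) = 0.3087
- n = (1.0289)² / 0.000818 = 1294.1
- 1294.1 / 0.80 = 1617.7, that is 1618

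The 20% loss is inferred. The radiographer sample fits the same inference: 0.63 against 0.88 gives 45.3 by the same formula, and 45/0.80 = 56.25. With 20% loss, 1618 is fully accounted for, so no design effect is left to be hidden in the figures that are not shown.

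**2. Power under independence.** Power = Φ{[d·√n − 1.96·√(2p(1−p))] / √(p1(1−p1) + p2(1−p2))}. With n = 1294 this is 80.0%; with n = 1618 it is 88.0%. The surplus over 1294 is the allowance for lost images.

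**3. Clustering by radiographer.** Design effect DE = 1 + (m − 1)·ICC, with n replaced by n/DE. The ICCs are assumptions; the documents give none.

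| Images analysed | m | Power, ICC 0.01 | Power, ICC 0.02 | Power, ICC 0.05 |
|---|---|---|---|---|
| 1618, nothing lost | 1618/56 = 28.9 | 79% (DE 1.28) | 71% (DE 1.56) | 53% (DE 2.39) |
| 1294, images lost, 56 radiographers remain | 1294/56 = 23.1 | 72% (DE 1.22) | 65% (DE 1.44) | 49% (DE 2.10) |
| 1294, about 20% of radiographers lost | 28.9 | 70% (DE 1.28) | 61% (DE 1.56) | 44% (DE 2.39) |

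The second row matches the article's description of the loss as a loss of images. If all 1618 are analysed, power stays at or above 80% while DE is at most 1618/1293 = 1.251, that is up to a radiographer ICC of 0.251/27.9 = about 0.009. At 1294 there is no such margin.

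**4. Clustering by hospital, for illustration.** This assumes a post-intervention comparison only and normal quantiles. With 2 hospitals per group, the variance of the difference rises by SD²/2 + SD²/2 = SD². Hence DE = 1 + SD² / [2 × 0.0727 × 0.9273 / n].

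| Between-hospital SD | Power, n = 1618 | Power, n = 1294 |
|---|---|---|
| 0.5 point | 78% (DE 1.30) | 71% (DE 1.24) |
| 1.0 point | 56% (DE 2.20) | 52% (DE 1.96) |
| 1.36 points | 42% (DE 3.2) | 39% (DE 2.8) |

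The last row converts the cited range over 3 hospitals: (9.7 − 7.4)/1.693 = 1.36 points. It is an upper-end reading, because the range includes sampling error and covers examinations other than chest radiographs.

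Two limits follow from having 2 hospitals per group. The effective number per group cannot exceed 2/ICC, so in this post-only comparison a hospital ICC above 2/1293 = about 0.0015 cannot be offset by more images. And a hospital-level test has 2 degrees of freedom, with a critical value of 4.30 instead of 1.96, so the normal-quantile figures are favourable.

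**The case against.** **Power might still reach 80%.** If no image is lost and only radiographers cluster, 1618 holds 80% up to an ICC of about 0.009. The figure is also a minimum. If radiographers averaged 50 images each (an assumption; 56 × 50 = 2800 per group), power under radiographer clustering alone would be about 92%, 83% and 60% at ICCs of 0.01, 0.02 and 0.05. This stands as a reason not to say that the study certainly falls short. It does not restore the stated basis, since the surplus is set aside for lost images and extra images do little against hospital clustering.

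**A reader might infer that the study has only about 40% power.** The documents do not support that. The figure turns a three-hospital range from another study, over all examinations, into an SD and applies it to a post-only comparison. The plan has a baseline, two follow-up assessments and a repeated-measures analysis. Stable differences between hospitals largely cancel in a change contrast; what then matters is how much hospitals differ in their change, which is not given. A change contrast also has its own larger sampling variance, so this argument does not show that power is adequate.

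**Matching.** Exact matching on five radiographer characteristics may reduce radiographer variation between groups. It does not remove differences between hospitals, and the calculation does not use it.

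**The design is constrained.** Only 5 hospitals exist in the region, and the Limitations section concedes weaker causal inference for want of randomization. That concession concerns bias; the point here concerns variance and power.

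**Conclusion.** The point holds in this form: 1618 per group rests on independent radiographs, and the implied 80% power is conditional on that. It is a fault in a design assumption. The arithmetic itself reproduces, so a reader should not infer a calculation error.

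At about 1294 analysed images, any positive ICC takes power below 80%. How far below depends on ICCs that the documents do not give. Over assumed radiographer ICCs of 0.01 to 0.05, power runs from 79% to 53% with all 1618 images and from 72% to 49% with 1294 images from 56 radiographers. Hospital variation adds to the shortfall; the figures for it are illustrative only. The 80% is therefore not assured. That it is certainly missed in every scenario would be too strong.

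**What to change.** In the Sample Size section:

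1. State that 1618 per group gives 80% power, after the image loss allowed for, only if radiographs are independent, and state the loss rate used.
2. Give design effects for radiographer (about 29 images each, or about 23 after loss) and for hospital (about 809 each), over a stated and justified range of ICCs. If the primary analysis is of change from baseline, base the hospital term on variation in change.
3. Replace the implied 80% with the resulting range of power, or with the difference detectable at 80%.
4. Acknowledge the limit set by 2 hospitals per group, including the 2 degrees of freedom.

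No added hospitals or radiographers are requested. The cost is a few sentences and a less favourable power figure.

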**Figure 2 figure2:**

Formula of sample size estimation to test a hypothesis of proportion of 2 populations.

**Figure 3 figure3:**

Sample size of the secondary outcomes.

**Figure 4 figure4:**

Sample size of the primary outcome.

### Instruments

A questionnaire developed by the researcher based on the information motivation behavioral skills model is one of the instruments that will be used to evaluate the level of radiographer knowledge about imaging, as well as the motivation and skills. It consists of close-ended questions and is divided into 2 sections: demographic data of the radiographer and domain of the radiographer’s knowledge, motivation, and skills. Radiographers are expected to spend 5 minutes completing the questionnaire.

A check list was recommended and used in several studies around the world to measure the repetition rate of routine digital chest radiographs [8]. It is an international instrument. It contains radiographer demographic data, number of radiographs performed by radiographer, number of repeated radiographs, and causes of repetition. It is completed by the researcher in order to obtain accurate results and overcome biases, using actual numbers. Therefore, its reliability does not need to be checked. Furthermore, studies conducted by Al-Malki et al [12] and Khafaji and Hagi [11] in Saudi Arabia used the same instrument. This means that the check list used in this study is valid.

In order to achieve accurate and precise results, the validity and readability of the questionnaire will be evaluated. Face validity will be ensured by an expert currently practicing to ensure the veracity of the meaning, wording, and sequences. Content validity will be ensured by lecturers working in the university to ensure clarity, representation, and comprehensiveness. Furthermore, factor analysis will be conducted to ensure a structural correlation between variables and factors on the instruments. Finally, reliability through the Cronbach coefficient alpha will be conducted to ensure internal consistency.

### Intervention

Piloted intervention will be used in this study. The intervention is in the form of printed educational material distributed to routine digital radiographers in the departments of intervention hospitals based on a specific module developed for the purpose of the study. The intervention module was developed from previous studies [36-39]. The education material was developed based on the information motivation behavioral skills model. This model has 4 constructs: information, motivation, skills, and behavioral change. This model was selected because it was recommended by another researcher to study the effect of self-efficacy, attitude, and knowledge on repetition. The intervention component comprises 3 sections. The first section touches on the background of the repetition issue and the importance of producing high-quality chest images. The second section encompasses the motivation issue of repetition and dose of radiation. The third section includes important skills that should be performed by a radiographer to reduce the repetition rate of chest images. Furthermore, the educational material discusses the issue of repeated radiography and the definition, repetition rate, international standard, causes of repetition, and the burden of repeated radiography to radiographers, patients, clinicians, and the organization. Anatomical parts which should be included in chest radiography will also be included in the education material.

### Outcome Measure

#### Primary Outcome

The primary outcome of this research is the repetition rate of routine digital chest radiographs. It is the change of the behavior based on the information motivation behavioral skills model.

#### Secondary Outcome

The secondary outcome in this study is knowledge, motivation, and skills of radiographers. Based on the information motivation behavioral skills model, there are direct and indirect correlations between knowledge and behavioral change. There are also direct and indirect correlations between motivation and behavior change. Meanwhile, behavioral skills have a direct correlation with behavioral change.

### Statistical Analysis

Data analysis in this study is divided into 2 parts: descriptive and inferential. Descriptive data will be calculated in order to compute the central tendency and dispersion to add valuable statistical information to the study. Inferential data analysis will be used to meet a specific objective. Chi-square, 1-way multivariate analysis of variance, 2-way repeated measure multivariate analysis of variance, and multivariate analysis of covariance are the statistical methods that will be used to test the hypothesis. *Cochran Q test* will be also employed to assess the difference in proportion. The level of significance will be set at α=0.05, and all testing of hypotheses will be conducted using 2-sided tailed hypotheses. The statistical program used is SPSS version 22 (IBM Corp).

### Ethics Approval and Registration

Approval from the ethics committee of the faculty of Medicine and Health Sciences of the University Putra Malaysia was obtained (reference number EXP16 P160). Approval to conduct the study was also obtained from the Ministry of Health (reference number H-02-J002). Approvals from Makkah health affairs and the hospitals that are under study were also obtained. In addition, radiographers who will be involved in the study will sign a consent form.

## Results

The researchers expect that the repetition rate and the radiographer knowledge, motivation, and skills in both the control and intervention groups before intervention are statistically not significant (*P*>.05). It is expected that a high repetition rate with a low level of knowledge, motivation, and skills in both groups will be found in the baseline data. We predict that after implementation of the educational material in intervention hospitals, the knowledge, motivation, and skills of radiographers will increase and the repetition rate will *reduce* (*P*<.05), but we do not expect the repetition rate, knowledge, motivation, and skills to change in the control group (*P*>.05). It is expected that the intervention will be effective to change the behavior and reduce the repetition rate of routine digital chest radiography (*P*<.05). The results are expected to be published in 2018.

## Discussion

### Summary

This quasi-experimental time series with control group aims to investigate the effect of printed educational material on radiographer knowledge, motivation, and skills and the radiography repetition rate.

Educating radiographers helps reduce the dose of radiation exposure on patients, decreases waiting time, and increases patient satisfaction. A reduction in the repetition rate decreases the dose of radiation and reduces the workload. This intervention is significant to the organization as it reduces the burden of equipment consumption and cost as well as assists the organization in achieving its vision and goals. In addition, implementing an educational program that focuses on reducing the repetition rate of radiographs has been highly recommended [12,40,41].

To our knowledge, this is the first study that combines 4 outcome variables—knowledge, motivation, skills, and the repetition rate of routine digital chest radiography—and aims to investigate the effect of using printed educational material on the repetition rate of routine digital chest radiography. Furthermore and based on our knowledge, this is the first study that analyzes the repetition rate among radiographers.

The intervention module will be made available in both English and Arabic languages, and participants can choose their preferred language to complete the sessions. The intervention program was designed to be as brief as possible to increase readability. The printed educational material was selected because of the difficulty of assembling radiographers from different cities in one place at one time. There is a need to overcome the issue of bias to increase the credibility of the study. The quasi-experimental design is one of the strongest designs for this particular research.

